## Discussion

### Limitations

This study protocol has several limitations that should be acknowledged. First, although efforts will be made to minimize contamination bias, it is not possible to fully restrict students in the control group from engaging in tennis-themed sports video gaming independently outside the study setting. Such exposure may introduce variability and potentially dilute the observed intervention effects. In addition, variability in participants’ prior experience with video games or gaming consoles may influence engagement and learning, introducing heterogeneity in intervention effects. Differences in teaching style and classroom environment may also affect the consistency and fidelity of intervention delivery. The relatively short duration of the intervention may further limit the ability to observe long-term changes in physical literacy or sustained physical activity behaviors.

Measurement-related constraints also warrant consideration. The study relies on self-reported measures for physical activity and gaming behavior, which are subject to recall bias and social desirability bias and may affect data accuracy. Moreover, participants’ awareness of being observed during the intervention may lead to the Hawthorne effect, where behavior changes occur simply because of observation rather than the intervention itself. These factors should be considered when interpreting the findings. Performance-based assessments can carry measurement error and may not fully capture the breadth of PL in authentic contexts. Specifically, the study assessed selected perceptual-motor components (simple reaction time and eye-hand coordination) rather than comprehensive motor competence, which limits interpretation of PL development to specific attributes. The reliance on self-reported measures introduces potential biases that should be interpreted with caution. The tennis knowledge quiz used in this study was developed by the research team and pilot-tested for clarity and relevance. However, it has not been formally validated, which may introduce measurement bias and limit the generalizability of findings related to cognitive domain outcomes. Future studies should consider using or developing standardized, validated instruments to assess sport-specific knowledge.

Additionally, we acknowledge that the measures of cognitive and social engagement employed in this study are exploratory and context-specific. These constructs, such as attention, decision-making, peer interaction, and collaboration, are complex and multidimensional, and currently lack universally validated instruments for use in SVG interventions within PE settings. Our intention in including these measures was to provide preliminary insights into how students engage beyond physical outcomes, which we believe is critical for understanding the broader educational value of such interventions. However, we recognize that these findings should be interpreted with caution and may not be generalizable to other contexts. Future research should prioritize the development or adoption of standardized, validated tools that can reliably capture cognitive and social engagement across diverse populations and learning environments, and examine how these dimensions contribute to long-term educational and developmental outcomes.

### Theoretical contribution

This work aims to extend PL theory by exploring its application within technology-enhanced learning environments. Current frameworks primarily emphasize traditional pedagogical approaches, with limited consideration of digital tools. By incorporating SVG into structured PE lessons, this study seeks to demonstrate how interactive technologies can operationalize all four domains of PL: physical, cognitive, affective, and social, within a hybrid learning context. The inclusion of the social domain, assessed through the APLQ subset, addresses a notable gap in existing literature where social engagement is often underrepresented. These insights are expected to inform conceptual models that position digital interactivity as a legitimate pathway for physical literacy development.

### Practical implications

If successful, this intervention could provide educators with a novel strategy to enhance student engagement, motivation, and collaborative learning in PE settings. SVG-based activities may serve as an inclusive tool for students who are less confident in traditional physical activities or who respond positively to gamified experiences. The protocol also emphasizes alignment with curriculum objectives and classroom management considerations, which are critical for real-world implementation. Future research will be needed to evaluate long-term impacts on physical literacy and physical activity behaviors, as well as to refine best practices for integrating technology into PE curricula.

### Confidentiality

All data collected during the study will be handled with strict confidentiality. Informed consent will be obtained from all participants, and data will be anonymized using unique identifiers. The sample of the consent form is attached as Appendix 3. Personally identifiable information, such as names and contact details, will be stored separately from research data and excluded from all analyses and publications.

Data will be retained for five years, after which personal identifiers will be securely disposed of. Secure data collection methods—including encryption and restricted access protocols—will be employed to safeguard data integrity. Access to raw data will be limited to authorized members of the research team.

No data will be shared with third parties without explicit participant consent. Any data shared for academic or collaborative purposes will be fully anonymized. Participant confidentiality will be maintained throughout the research process and beyond.

### Data monitoring

The principal investigator (PI), along with designated research assistants, will oversee data monitoring throughout the study. Interim analyses will be conducted at predefined intervals to evaluate the efficacy and safety of the intervention. Any anomalies or unexpected patterns will be promptly investigated and reported to the PI. Based on the interim findings and other relevant considerations, the PI will determine whether to continue or terminate the trial. This decision-making process will follow established protocols and ethical guidelines [28].

### Patient and public involvement

Students were not involved in the initial design of this study. Both students and teachers will participate in the conduct, reporting, and dissemination phases. Teachers from the tennis classes involved in the study contributed to its design and will continue to be engaged through regular meetings to provide feedback and insights as the study progresses.

### Protocol amendments

Any modifications to the study protocol, including changes to eligibility criteria, outcomes, or interventions, will be communicated to the Survey and Behavioural Research Ethics Committee of the CUHK and to trial participants via email. These changes will be discussed and approved by the PI prior to implementation.

### Harms

Tennis class teachers involved in the study will be responsible for identifying, documenting, and reporting any adverse events or unintended effects related to the trial interventions. All incidents will be recorded in a pre-designed Excel file for systematic tracking and future reference. In the event of any such occurrences, appropriate healthcare professionals will be contacted immediately to provide assistance. Although the likelihood of musculoskeletal or other injuries from sports video gaming is low, minor adverse events such as discomfort, fatigue, or strain may still occur. In particular, physical testing procedures such as the Alternate Hand Ball Toss Test may pose a slight risk of upper limb strain or coordination-related discomfort due to repetitive movements. All minor adverse events will be categorized by type, severity, and relation to either the intervention or testing activity, and reviewed regularly by the research team to ensure participant safety and transparency throughout the study.

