The intervention is designed to be flexible, allowing it to enhance rather than replace traditional PE instruction. Since the SVG does not require formal teaching and students engage with the game independently, it can be integrated as a supplementary activity outside of scheduled PE class time. This approach enables students to reinforce and extend their learning of tennis-related concepts without interfering with the core instructional time allocated for physical skill development. The SVG provides additional opportunities for cognitive engagement and sport-specific knowledge acquisition, supporting the broader goals of PL.

Despite growing interest in the educational and motivational potential of SVGs, intervention studies utilizing these tools to promote PL remain limited, particularly in Asian contexts [17]. Most existing research has been conducted in Western settings, leaving a gap in understanding how culturally relevant applications of SVGs may influence PL and physical activity behaviors in Asian populations.

Therefore, the aim of this study is to investigate the effectiveness of a tennis-themed SVG intervention, implemented alongside regular PE lessons, in promoting holistic PL among university students in Hong Kong. Specifically, the study will evaluate whether SVG participation can enhance motivation, sport-specific knowledge, physical competence, social engagement, and physical activity engagement. Using a cluster randomized controlled trial design, this research seeks to identify innovative, technology-enhanced strategies to improve PE outcomes and foster lifelong physical activity.

Following the intervention and subsequent follow-up, we hypothesize that:

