### Intervention

A six-week tennis-themed SVG intervention will be implemented for participants in the intervention group, supplementing their regular tennis PE lessons. This intervention is designed to align with the study’s goals of promoting PL and enhancing physical activity engagement among university students in Hong Kong.

A dedicated **“SVG Corner”** will be set up in a classroom, equipped with two PlayStation 5 consoles, each connected to four controllers and a monitor. Participants will engage with the tennis-themed SVG ‘*TopSpin 2K25’*, released in April 2024, which is known for its highly realistic gameplay, including accurate physics, player movement, and court dynamics. This realism helps bridge the gap between virtual and physical tennis, making it a suitable tool for reinforcing PL concepts such as spatial awareness, timing, and movement strategies. The game includes tutorials and skill challenges that provide structured learning opportunities aligned with specific PL goals. For example:

1. **Physical Competence**:

Gameplay requires fast reaction time and eye-hand coordination, simulating real tennis movements and decision-making. These elements promote motor skill development, agility, and movement control, which are core aspects of physical competence.

2. **Motivation**:

The immersive and gamified nature of *TopSpin 2K25* enhances enjoyment and engagement. By offering a fun and competitive environment, the intervention aims to boost students’ overall interest and motivation in real-life sports, supporting long-term physical activity participation.

3. **Knowledge and Understanding**:

In-game tutorials and challenges help students understand tennis rules, tactics, and movement principles, reinforcing cognitive engagement with physical activity.

4. **Social Interaction**:

Multiplayer modes (singles and doubles) promote peer interaction, cooperation, and friendly competition, which are important social dimensions of PL.

To support accessibility and adherence, at least one research assistant or student helper will be present during operating hours to manage the SVG Corner and assist participants. Clear and concise control guidelines will be displayed in the SVG Corner for easy reference. To maintain the integrity of the intervention, no formal tennis instruction will be provided during gaming sessions.

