Each participant in the intervention group will be required to attend two 20-minute gaming sessions per week, in addition to their regular PE classes. The SVG Corner will be open Monday to Friday, from 10:00–13:00 and 14:00–18:00. Due to equipment limitations (2 consoles with a total of 8 controllers), each session has limited quota. If a session reaches its quota due to the first-come-first-served arrangement, we will arrange an alternative time slot to accommodate affected participants. The attendance will be tracked weekly, in case where participants are unable to fulfill the attendance requirement, we will contact them via email to arrange make-up sessions. This ensures that all participants can fulfill the attendance requirement and receive the full intended dosage of the intervention.

To minimize contamination bias, students in the control group will not be provided access to the SVG Corner and will be advised not to engage in tennis-themed sports video gaming independently during the study period. While we cannot fully restrict external gaming behavior, participants will be informed of the importance of maintaining their assigned condition and asked to report any SVG-related activity outside the study. This will help us monitor potential crossover and account for it in the final analysis.

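### Adverse events are assigned to class teachers, but gaming takes place outside lessons under staff with no stated adverse-event duty, so minor gaming-related events may be under-recorded

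*Protocol article*

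**What the plan says.** The Harms section names one group to find and record harms: "Tennis class teachers involved in the study will be responsible for identifying, documenting, and reporting any adverse events or unintended effects" of the trial interventions. Events go into a prepared Excel file. Healthcare professionals are to be called at once when an event occurs. Minor events are to be classified by type, severity and whether they relate to the intervention or to the testing, and the research team reviews them regularly. The section expects injury from gaming to be unlikely but allows for discomfort, fatigue or strain.

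The Introduction describes the game as a "supplementary activity outside of scheduled PE class time". Under Intervention, the SVG Corner "will be set up in a classroom, equipped with two PlayStation 5 consoles", and on staffing the text reads "at least one research assistant or student helper will be present during operating hours to manage the SVG Corner and assist participants". On hours it reads "The SVG Corner will be open Monday to Friday, from 10:00–13:00 and 14:00–18:00". Each intervention student attends two 20-minute sessions a week on top of regular PE classes, and the control group has none.

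Under Eligibility criteria and recruitment, the workshop for research assistants and student helpers is described as covering how to play the game and how to run the sessions. Under Data monitoring, the principal investigator and designated research assistants oversee monitoring, and "Interim analyses will be conducted at predefined intervals to evaluate the efficacy and safety of the intervention".

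**The concern.** The duty to detect harms sits with people who, on the article's description, are not where the intervention is delivered. The people who are there have no stated part in recording harms. Followed as written, an event during a gaming session enters the log only if the student later tells a teacher, or if a helper passes it on without being asked to.

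The events the article foresees are mild and brief, and these are the least likely to be mentioned at a later lesson. The gap also falls on one arm only, since controls do not play. At stake are the completeness of the harms log, the soundness of the relatedness classification, and one input to the safety part of the interim review.

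**Working it through.** The plan states no figure on this point, so there is none to reproduce. The check sets the sections side by side, and the only arithmetic is planned exposure.

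1. **Who holds the duty.** Tennis class teachers (Harms).

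2. **Who is at the gaming site.** At least one research assistant or student helper (Intervention). No section places a teacher there. The site is open 3 + 4 = 7 hours a day on 5 days, or 35 hours a week, with places taken first come, first served. The classes all have different teachers (Randomization). Nothing ties a session to a student's own teacher.

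3. **Whether gaming overlaps with lessons.** The Introduction, Study design and Intervention sections all make gaming additional to PE lessons. The Abstract and the Theoretical contribution section speak more loosely of the game as part of PE lessons, but they set out no procedure. The operational sections govern.

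4. **Whether site staff have any adverse-event duty.** None is stated. Intervention has them manage the room and help participants. The workshop content as described does not mention adverse events. Data monitoring gives designated research assistants a general monitoring role with escalation of anomalies, but does not mention adverse events at gaming sessions, and it does not name student helpers.

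5. **Fit with the Harms section's own requirements.** Calling a healthcare professional at once requires someone present to act, and the named person is not described as present. Classifying an event as due to the intervention or to testing would be done by someone who did not see the session.

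6. **Planned exposure.** Inputs: 88 intervention students and 6 weeks (Study design); 2 sessions a week of 20 minutes (Study design and Intervention).
   - Sessions: 88 x 2 x 6 = 1,056 participant-sessions.
   - Time: 1,056 x 20 min = 21,120 min; 21,120 / 60 = 352 participant-hours.
   - Per student: 2 x 6 = 12 sessions; 12 x 20 = 240 min = 4 hours.
   - Control arm: 0.

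7. **What cannot be computed.** The article gives no adverse-event rate and no basis for the share of events a student would later report to a teacher. The 1,056 sessions measure exposure, not missed events.

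8. **What lies outside the gap.** The physical tests take place in scheduled PE lessons in both arms (Data collection), so test-related events are not affected by where the gaming is held.

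**The case against.** **Responsibility is not the same as eyewitness.** Making teachers accountable does not bar others from passing events on. Teachers keep meeting the same students in lessons, remind them to attend sessions, and have regular meetings to give feedback during the study. A student with lasting discomfort can report it then. This stands. A reader might infer that harms of gaming will be missed, or that every session goes unobserved by the responsible person by design. The article does not support either: later reporting is open, and the absence of teachers from the SVG Corner is a strong inference, not a stated fact.

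**Other routes exist.** Research assistants have a monitoring role, attendance is tracked weekly with email contact when sessions are missed, and physical discomfort is a listed reason to withdraw. These may bring the more troublesome events to light. They are not adverse-event recording, and the research team's regular review covers only what has been entered.

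**The risk is low.** The article says so for gaming, and it singles out the ball-toss test as the particular source of strain. That limits the importance of the point but does not explain why the duty is given to people not described as present.

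**Detail may be in the full protocol.** The article refers to a full protocol that is not at hand. Mere silence would be no finding. Here the article does assign the duty to a named group, and that assignment does not match its own account of delivery.

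**Asking at every session would bring its own bias.** Up to 12 prompts for each intervention student and none for controls would make ascertainment unequal between arms. This is right, and the fix below avoids it.

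**Conclusion.** The point holds in a limited form. The Harms and Intervention sections do not fit together: the named reporters are not among the staff described at the gaming site, and those staff have no stated adverse-event duty. Minor, transient gaming-related events may be under-recorded, and their relatedness judged second-hand, in the one arm that has 1,056 planned participant-sessions. How many events would be lost cannot be derived from the article.

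This rests on two assumptions: that teachers do not routinely attend the SVG Corner, and that no instruction outside the article already gives its staff a recording duty.

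A reader might go further and conclude that a report of no adverse events could not be trusted, or that the decision to continue or stop would rest on a defective log. The article does not support this. The activity is seated, short and low in risk; students remain in contact with teachers; and the principal investigator weighs other considerations besides the interim findings. No hypothesis, outcome or sample size depends on the log. The change is still worth making before the trial starts, because it improves safety capture at almost no cost.

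**What to change.** Reconcile the Harms and Intervention sections:

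- State in Harms that the research assistant or student helper on duty records any adverse event they observe or are told of during a gaming session, in the same Excel file. Include this in the staff workshop already planned.
- Keep teachers responsible for events in lessons, and record place and arm for each event.
- For comparing arms, add one identical adverse-event question to the questionnaire for both arms at post-intervention and follow-up, and base the comparison on that question. Do not prompt the gaming arm session by session.

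The cost is a sentence or two in the protocol, a few minutes of training and one extra questionnaire item at two time points. No new staff are needed, because the SVG Corner is already staffed whenever it is open. Events logged at the SVG Corner will still come from one arm only, so they should be reported descriptively.

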## Abbreviations

AHWT: Alternate Hand Wall Toss test
ANOVA: Analysis of Variance
APLQ: Adolescent Physical Literacy Questionnaire
CUHK: The Chinese University of Hong Kong
ICC: Intra-cluster Correlation
IPAQ-SF: International Physical Activity Questionnaire – Short Form
MANCOVA: Multivariate Analyss of Covariance
OSF: Open Science Framework
PE: Physical education
PI: Principal investigator
PL: Physical literacy
PPLI: Perceived Physical Literacy Instrument
RDT: Ruler Drop Test
SMD: Standardized mean difference
SMS-6: Sport Motivation Scale-6
SPIRIT: Standard Protocol Items: Recommendations for Interventional Trials
SVG: Sports video game.
